## Dose escalation schedule

In every cohort, subjects will be dosed at least 30 minutes apart. In cohorts C2, C3 and C4, 1 participant will receive a sentinel dose prior to the remaining 7 participants being dosed. Minimum time-periods of observation between dose escalations are summarised in
Figure 1a and
Figure 1b.

**Figure 1a. f1a:**
[figure not shown]
Single Dosing Escalation Strategy.

**Figure 1b. f1b:**
[figure not shown]
Multiple dosing escalation strategy. DSMB, Data and Safety Monitoring Board; IV, intravenous administration; PO, oral administration. Days represent the minimum period between dose escalations. Longer intervals may be required. Time interval until DSMB meetings represent the earliest possible meeting and later meetings may occur.

C2 begins with a sentinel dose and the remaining 7 subjects will be dosed at least 24 hours after this. C3 will begin with a sentinel dose and the remaining 7 subjects will be dosed 72 hours after this. Cohort C4 will be dosed a minimum of 1 week after C3 and will also commence with a sentinel dose followed by 3 days until the remaining 7 subjects are dosed. The CIV cohort will be dosed in tandem with C3. Dose escalation decisions will not be dependent on the results of the pharmacodynamic assay, as this analysis is exploratory and has not been validated. Between the single dosing stage and the multiple dosing stage, preliminary pharmacokinetic data will be made available
*.* Multiple dosing will only proceed once the DSMB have reviewed adequate pharmacokinetic data from the single dosing stage to be satisfied that the proposed dosing regimen will not lead to accumulation of the study drug. A minimum of one week after the final dose is given in CM1, dosing of CM2 will commence. The flowchart (
Figure 1) summarises the process of dose escalation.

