### Dose

Participants will be dosed in cohorts of 8. Cohorts for single oral doses are abbreviated as ‘C’, single intravenous dose cohorts as ‘CIV’ and multiple oral dosing cohorts as ‘CM.’ There will be four single ascending oral dosing cohorts (C1-C4), two intravenous dosing cohorts (CIV1 and CIV2) and two multiple dosing cohorts (CM1 and CM2). The anticipated dose escalations are summarised in
Table 2. The dosing regimen in
Table 2 represents the anticipated dose escalations that will be followed should the DSMB have no safety concerns. The highest single oral dose of unithiol that will be administered is 1,500 mg. Any increase above 1,500 mg would require approval from the Sponsor and the ethics and regulatory committees. Following review by the DSMB, dose levels may be repeated, smaller increments in dose escalation may be adopted or dose levels may be lower than the preceding dose level and, therefore, additional cohorts may be included. The DSMB will make these decisions based on adverse event data.

**Table 2. T2:** Summary of dosing regimens.

Single dosing *(and CIV1)*		
Cohort name	Number of subjects	Dose
C1	8	300 mg oral
C2	8	900 mg oral
C3	8	1200 mg oral
C4	8	1500mg oral
CIV1	8	3 mg/kg intravenous single dose
Multiple dosing *(and CIV2)*		
CM1	8	300–1200 mg oral qds for 2 to 3 days
CM2	8	1500 mg oral (or highest tolerated dose from single dosing) qds for 2 to 3 days
CIV2	8	Depends on emerging data (5–10 mg/kg intravenous) single dose

Additional dosing cohorts may be added depending on emerging safety data. Eight cohorts and the above dose escalations represent the maximum dose increases that would occur assuming reassuring safety data.

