### Justification for the proposed dose, route of administration, dosage regimen and treatment period

The starting dose for the oral single ascending dose stage will be 300 mg. This is a routine dose recommended for the treatment of heavy metal poisoning
^
38,
39
^. The maximum dose that will be administered during the oral single ascending dose stage will be 1,500 mg. This dose has been selected based on pre-clinical in-vitro assays that have shown that high concentrations of unithiol are required to inhibit the pro-coagulant effects of snake venom
^
21
^. In this experiment, 150 µM of unithiol was required to prevent consumption coagulopathy. Given that previous in-human pharmacokinetic analysis has identified a C
_max_ of 25 µM following administration of 300 mg oral
^
33
^, it has been estimated that a dose of 1,500 mg would be required to achieve a peak plasma concentration sufficient to inhibit coagulopathy. Published reports of dose levels of unithiol equivalent or higher than 1,500 mg oral suggest that this dose is safe
^
24,
31,
32
^.

The dose that will be given to the first intravenous dosing cohort (CIV1) will be 3 mg/kg. This has been selected as it is at the lower range of the routinely recommended dose for acute heavy metal poisoning (3–5 mg/kg)
^
27,
40
^. Previous pharmacokinetic analyses have shown that 3 mg/kg intravenous achieves an initial plasma concentration of 100 µM
^
27
^. At least one further intravenous dosing cohort will be included. The dose administered will be decided by the DSMB based on emerging data from the first stage of the trial. This dose is expected to be 5 mg/kg, although a dose of up to 10 mg/kg may be selected, depending on emerging safety and pharmacodynamic data.

For the multiple dosing cohorts (CM1 and CM2), the study team will select doses that show the optimum profile for treating snakebite, based on safety, tolerability and any available pharmacokinetic and pharmacodynamic data. If the pharmacodynamic data shows a dose response relationship and is deemed to demonstrate sufficient reliability, the investigators will aim to select CM1 based on a minimum dose associated with adequate

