### Pharmacodynamics

An exploratory outcome is to assess the efficacy of unithiol to inhibit the pathogenic actions of venom,
*ex vivo*. If the pharmacodynamic assay produces results that are deemed reliable, then pharmacodynamic data from the single dosing stage could be used to guide the dosing regimen for the multiple dosing stage. If the pharmacodynamic assay does not produce useful results, then dose and dosing frequency decisions will be made based on safety and preliminary pharmacokinetic data.

*Ex vivo* assays will be developed for the purposes of establishing a dose-response and estimating a pharmacodynamic profile. These assays will rely on spiking subjects’ plasma with venom
*ex vivo* and measuring activity of snake venom metalloproteinases. These assays are being developed for the purposes of this study, and a published validated assay does not exist. It would not be appropriate to assign these assays as primary outcome variables as they are experimental and represent an indirect estimate of efficacy.

These assays will continue to be refined during this study. They primarily represent a tool to compare venom metalloproteinase inhibition between subjects receiving different doses of unithiol, rather than a direct measure of efficacy. Where possible, these assays will be conducted and refined in the laboratory facilities at KEMRI-CGMRC. Split samples will also be shipped to Liverpool School of Tropical Medicine Centre for Snakebite Research & Interventions (LSTM CSRI).

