### Pharmacodynamics

Pharmacodynamic outputs will vary between assay and are exploratory. For the fluorogenic substrate assay the area under the fluorescence-time curve will be compared between dosing groups using ANOVA and an appropriate post-hoc test (e.g., Tukey’s). The time to plateau and time to mid-point of fluorescence (Km) of the fluorescence-time curves will also be compared with this approach. These same measures will be calculated for the plasma clotting assay. Further assays will be developed, and analysis will be planned as appropriate.

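### The protocol bars the unvalidated pharmacodynamic assay from dose escalation decisions, yet lets pharmacodynamic data help set the second intravenous dose without any reliability condition

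*Protocol article*

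**What the plan says.** **Dose escalation schedule** (text after Figure 1b): "Dose escalation decisions will not be dependent on the results of the pharmacodynamic assay, as this analysis is exploratory and has not been validated". No exception is given.

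**Justification for the proposed dose**, on the second intravenous cohort: "The dose administered will be decided by the DSMB based on emerging data from the first stage of the trial". The expected dose is 5 mg/kg, but "a dose of up to 10 mg/kg may be selected, depending on emerging safety and pharmacodynamic data".

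**Dose**, Table 2: CIV1 receives 3 mg/kg. The CIV2 entry reads "Depends on emerging data (5–10 mg/kg intravenous) single dose". The text introducing the table and the note below it both describe its contents as dose escalations, and the note covers all eight cohorts. On repeated levels, smaller increments, lower levels and added cohorts, the same section says "The DSMB will make these decisions based on adverse event data".

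**Multiple dosing.** The dose justification allows CM1 to be chosen on ex vivo inhibition only if the assay shows a dose response and is judged reliable enough. The Pharmacodynamics section under Assessment of pharmacokinetics and pharmacodynamics repeats that condition. It falls back on safety and preliminary pharmacokinetic data if the assay is not useful.

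**The assay and its analysis.** The same Pharmacodynamics section gives comparison between doses as the assay's main purpose and says "These assays will continue to be refined during this study". Under Statistics, the area under the fluorescence-time curve "will be compared between dosing groups using ANOVA and an appropriate post-hoc test". A cut-off of p ≤ 0.05 applies to any comparison.

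**The concern.** The step from CIV1 to CIV2 raises the intravenous dose in healthy volunteers. One section tells the DSMB that such decisions do not depend on the pharmacodynamic assay, and gives lack of validation as the reason. Another names pharmacodynamic data as a basis for this same step, without requiring that the assay first be found reliable. A board following one section would depart from the other. A SAP could not resolve this, because both statements are in the protocol and both concern dose selection.

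The second issue concerns interpretation. Cohorts are dosed consecutively and there is no placebo group. If the assay changes between cohorts and the reported results carry that change, the difference between dosing groups mixes assay version with dose.

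**Working it through.** **1. The contradiction, set side by side**

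| Question | Dose escalation schedule | Justification for the proposed dose |
|---|---|---|
| May pharmacodynamic results bear on the decision? | No, for dose escalation decisions | Yes, together with safety data, for CIV2 |
| Condition on assay reliability? | Not applicable, as use is barred | None for CIV2; stated for CM1 |

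Is CIV2 a dose escalation? It goes up from CIV1, and Table 2 lists it among the cohorts that its note calls dose escalations. By the protocol's own usage it is, so the bar applies to it.

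Size of the step: 5/3 = 1.7 times CIV1 at the expected dose, and 10/3 = 3.3 times at the ceiling.

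**2. The conditional drift issue**

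Inputs from the protocol: 8 participants per cohort; five cohorts in the single-dose part of Table 2 (C1 to C4 and CIV1); ANOVA between dosing groups; cut-off 0.05. The protocol's total reproduces: 8 cohorts × 8 = 64. The protocol gives no assay drift figure and no within-cohort SD, so the shift sizes below are assumptions.

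Model: no true dose effect, and each cohort's assay level shifted at random with SD *s*, in units of the within-cohort SD, with a separate assay version per cohort. The F statistic is then scaled by 1 + 8*s*². With 4 and 35 degrees of freedom the critical value is 2.64, so the rejection rate is P(F(4,35) > 2.64/(1 + 8*s*²)).

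| *s* (assumed) | 1 + 8*s*² | Threshold | Rejection rate |
|---|---|---|---|
| 0 | 1.00 | 2.64 | 5.0% |
| 0.25 | 1.50 | 1.76 | 15.9% |
| 1/3 | 1.89 | 1.40 | 25.5% |
| 0.5 | 3.00 | 0.88 | 48.6% |

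CIV1 is dosed in tandem with C3 and may share its assay version. Simulating four versions over the five cohorts gives about 15%, 23% and 44%. Restricting to C1 to C4 (F with 3 and 28 degrees of freedom, critical value 2.95) gives 14%, 22% and 42%.

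As an alternative pattern, take a single assay change between C2 and C3, using C1 to C4 only. A step of 0.5 SD gives 17.2% and a step of 1 SD gives 58.7% (noncentral F). With one assay version throughout, the rate is 5.0%.

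**The case against.** Three stronger readings are tempting, and the documents do not support them.

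- **That pharmacodynamic use for CM1 contradicts the bar in the same way.** That use is conditional on reliability in both places where it appears, with a fallback to safety and pharmacokinetic data, and the DSMB must review pharmacokinetic data before multiple dosing. It needs to be labelled as an exception, or as outside the bar, but it is not the same open conflict.
- **That the Dose section's reliance on adverse event data is a further contradiction on CIV2.** The decisions it refers to are repeated, smaller or lower dose levels and added cohorts. Table 2 in that section leaves CIV2 to emerging data.
- **That assay version is in fact confounded with dose.** The protocol says the assays will be refined during the study. It does not say that each cohort's reported results come from a different version. Duplicate storage is allowed for and split samples go to a second laboratory, so a single-version run is possible. The laboratory analytical plan and SAP, neither shown, may already require one.

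It can also be said that safety data remain a named basis for CIV2, that the DSMB decides, that 5 mg/kg is the expected dose, and that the pharmacodynamic objective is exploratory in a study not powered for group comparisons. All of this stands and limits the impact. None of it removes the conflict over what may inform the CIV2 dose.

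**Conclusion.** The CIV2 contradiction is established from the text and rests on no assumption. Two sections give incompatible bases for a dose step of 1.7 to 3.3 times CIV1. No view is taken here on which rule or dose is right. It should be corrected, and the remedy is wording.

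The drift point is a conditional risk to an exploratory outcome and not an established error. The 16% to 49% range depends on assumed shifts of 0.25 to 0.5 SD and on a separate assay version for each of five cohorts. It shows how sensitive the comparison would be and does not estimate what will happen. The primary safety outcome and the secondary pharmacokinetic outcome do not depend on the pharmacodynamic comparison.

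**What to change.** 1. **Reconcile the text.** Make the Dose escalation schedule and the dose justification agree, and align the Dose section and the Pharmacodynamics section with them. One statement should say whether, and under what condition, pharmacodynamic results may inform the CIV2 dose. It should also say whether the conditional use for CM1 is an exception to the bar. The cost is wording only, through the protocol's amendment process.

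2. **Unless the laboratory analytical plan or SAP already provides for it, fix the assay version for the reported comparison.** After the last cohort, run stored duplicate aliquots from all cohorts on one frozen version, with cohorts interleaved across plates. Base the between-dose analysis on that run and label earlier runs as developmental. The cost is one batch run. Storage time will differ between cohorts, so stability controls are needed on the plates. This step protects only the exploratory comparison. It comes too late to affect the CIV2 and CM1 choices, which depend on the first step.

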## Sample size determination

As this is a phase I clinical trial, with a primary aim to evaluate the safety of the escalating unithiol doses, a sample size calculation has not been conducted. Participants will be dosed in groups of eight, which is a commonly used design in phase I clinical trials
^
41
^.

The number of cohorts will be guided by the safety and tolerability of unithiol. Additional cohorts may be added if adverse events occur that, following review by the DSMB, warrant smaller increments in dose escalation or expansion at a dose level.

## Randomisation procedure

Subjects will be allocated to a dosing cohort using stratified permuted block randomization. Stratification will be according to sex and age. Following the screening visit (and prior to attendance at the in-patient facility), participants will be asked to attend to receive the results of the clinical investigations, to be informed of their eligibility and to be informed of their allocation following randomization. Throughout the study, a minimum of four participants (randomly selected) will be on stand-by for each dosing cohort – to replace any participants that cannot be dosed. There is no placebo group and therefore this is not a randomized controlled trial. Participants in dosing cohorts that involve sentinel dosing will undergo a second step of randomization, to allocate individuals for sentinel dosing. The study team member responsible for randomizing subjects will be blinded to the subject’s identity and any information related to the subject except for their sex and age. Once randomization is complete, cohort allocation will be unconcealed. The study team and the participants will not be blinded.

Enrolment into the trial will begin the night before dosing. The participant will be reviewed by a study team member in the in-patient facility. Any concerns or questions the participant may have will be answered. Any participants that do not arrive or cannot be dosed due to becoming ineligible (e.g., due to illness) will be replaced, as detailed below.

## Trial procedures

Table 3a and
Table 3b summarise the daily study procedures for the single and multiple dosing stages, respectively (additional assessments or blood draws may be added based on emerging data or if clinically indicated). Participants will be admitted to an in-patient facility the night prior to dosing and monitored until 24 hours after their last dose of unithiol and will be reviewed as an out-patient on days 2, 5 and 42 (with telephone follow-up at 6-months).

**Table 3a. T3a:** Study schedule – single dosing regimen.

Activity	Screening (Day -28 to Day -2)	Randomisation (Day -27 to Day -2)	Day -1	Day 0	Day 1	Day 2	Day 5	Day 42	6-month telephone visit
In-patient stay									
Informed consent									
Inclusion/exclusion criteria									
Demographic data (including smoking history)									
Medical history									
Viral serology									
Pregnancy test ^ a ^									
Provide results to investigations									
Randomization									
**Study residency:**									
Check in									
Check out					^ b ^				
Non-residential visit									
**Study drug administration**									
**Safety and tolerability:** ^ c ^									
Adverse event recording ^ d ^									
Vital signs (including blood pressure and pulse rate)									
Axillary body temperature									
12 lead ECG ^ e ^									
Clinical laboratory evaluations (including haematology, clinical chemistry, and urinalysis)									
Body weight (and height at first visit)									
Physical examination									
Concomitant medication									
**Blood sampling**									
Pharmacokinetics:									
Pharmacodynamics:									

**Table 3b. T3b:** Study Schedule – Multiple dosing regimen.

Activity	Screening (Day -28 to Day -2	Randomisation (Day -27 to -2)	Day -1	Day 0	Day 1	Day 2	Day 3	Day 5	Day 42	6-month telephone visit
In-patient stay										
Informed consent										
Inclusion/exclusion criteria										
Demographic data (including smoking history)										
Medical history										
Viral serology										
Pregnancy test ^ a ^										
Provide results to investigations										
Randomization										
**Study residency:**										
Check in										
Check out							^ b ^			
Non-residential visit										
**Study drug administration ^ f ^ **										
**Safety and tolerability:** ^ c ^										
Adverse event recording ^ d ^										
Vital signs (including blood pressure and pulse rate)										
Axillary body temperature										
12 lead ECG ^ e ^										
Clinical laboratory evaluations (including haematology, clinical chemistry, and urinalysis)										
Body weight (and height at first visit)										
Physical examination										
Concomitant medication										
**Blood sampling**										
Pharmacokinetics:										
Pharmacodynamics:										

ECG, electrocardiogram.
^a^ Females aged 18 to 64 years. Performed in urine. 
^b^ In house stay until 24 hours post-dose.
^c^ The timings of all measurements to be performed during the study may be subject to change based on the ongoing review of the safety, tolerability, pharmacokinetic and pharmacodynamic results.
^d^ Serious adverse events will be recorded from enrolment, and adverse events will be recorded from dose administration until the final follow up Visit.
^e^ Resting 12 lead ECG: at Screening; and Day 1 post dose and prior to discharge from inpatient facility. Additional ECG recordings will be taken at the discretion of the responsible clinician.
^f^ Doses anticipated to be administered four times per day for up to 72 hours.

## Procedures for collection of clinical samples

### Timing and volume of clinical samples

Figure 2a,
Figure 2b and
Figure 2c summarize the blood and urine sampling protocol for the single and multiple dose stages, respectively. The timing of blood and urine samples may be adjusted, and any such changes will be provided to the approval committees via a written notification. This would be because of emerging safety, pharmacokinetic or pharmacodynamic data.

**Figure 2a. f2a:**
[figure not shown]
Blood and urine sampling times and volumes during inpatient stay and out-patient follow-up – single oral dosing.

**Figure 2b. f2b:**
[figure not shown]
Blood and urine sampling times and volumes during inpatient stay and out-patient follow-up – single intravenous dosing.

**Figure 2c. f2c:**
[figure not shown]
Blood and urine sampling times and volumes during inpatient stay and out-patient follow-up – multiple oral dosing. βHCG, Beta-human chorionic gonadotrophin; D, day; NA, not applicable; RDT, rapid diagnostic test; PD, pharmacodynamics; PK, pharmacokinetics. Figure 2c is based on an assumed dosing duration of 30-hours. This may vary depending on emerging data and could extend up to a maximum of 72-hours.

### Justification of frequency and volume of blood sampling

Frequent blood sampling is required to understand the pharmacokinetic profile of unithiol. As this drug has a short-half-life, less frequent drug monitoring would lead to inaccurate estimates of the C
_max_ and AUC (area under the curve). For the pharmacodynamic analysis, it is important for us to understand the duration of efficacy. As unithiol is rapidly metabolised and excreted, the duration of venom inhibition may be short. By understanding this duration, better decisions of optimal dose frequency can be obtained. Blood volumes are based on required amounts for each assay, with the need for storage in duplicate being accounted for. Frequency of sampling and blood volumes may increase if adverse events occur or if the emerging pharmacokinetic or pharmacodynamic data demonstrate unanticipated findings. Nevertheless, the total blood volumes will not exceed 500 mL per 3 months, as per 2001 Kenya Ministry of Health Blood Transfusion Guidelines.

## Interim visits

Subjects will be admitted to the inpatient facility the day prior to dosing and monitored there by clinical study staff for a minimum of 24 hours following the last dose of unithiol. The rationale for this time window post dosing is based on the short half-life of unithiol, which is 4 hours, as well as the pre-existing safety data
^
33
^.

Subjects will be asked to visit the KEMRI-CGMRC or an appropriate facility on days 2, 5 and 42 for single dosing and days 5 and 42 for multiple dosing. They will be monitored for adverse events and have samples collected at these visits (
Table 3 and
Figure 2). The final planned review will be via telephone at 6 months (with the option for a face-to-face review, if necessary). If a participant cannot be contacted by telephone, arrangement for a home visit will be made, to ensure that the participant remains safe and well.

